### Data collection, management, and analysis

The MM *Detect and Detox* kit is an at-home sample collection service that participants will use to collect their own samples. The mailed kit has the following components: kit box, instruction card with activation code, sterile urine collection cup, biohazard bag with absorbent paper, pre-labeled polymailer. We have built a secure online portal for users to make accounts, register their kits, track the status of their samples, and view their testing results and feedback online. For the Lifestyle Audit, participants in the intervention group will schedule a Zoom call with a MM lifestyle coach to document the food, drinks they consumed, as well as all the products (personal care and household products) they used on the day prior to urine collection. MM’s technology team will oversee the security of MM’s software stack and servers, ensure that the platform is HIPAA-compliant, and oversee the software building and maintenance for this project.

Several emails will be sent to the participants to update them on their sample and report statuses and keep them engaged. FedEx Priority Overnight shipping will be used to ensure the sample quality. The turnaround time for the lab analysis and MM report generation is 2-4 weeks. Three months after submitting their baseline urine sample, participants will be sent the second kit and go through the same process again and submit their second samples. Detailed flow of events is illustrated in Fig. 1.

A third party, internationally well-known state-of-the-art laboratory is in contract with MM to perform the sample analysis. The lab staff will be blinded to participants’ identifiable information to ensure no bias will be introduced during sample analysis. The following common EDCs [75] are included in the panel: bisphenol A (BPA), detected in 95% of NHANES participants; [5] bisphenol S (BPS) and bisphenol F (BPF), detected in 89% of NHANES participants; [21]; low molecular weight phthalates, including mono-ethyl phthalate (MEP) and mono-n-butyl phthalate (MBP), metabolites of diethyl phthalate (DEP) and dibutyl phthalate (DBP); high molecular weight phthalates, including, mono(1-ethylhexyl) phthalate (MEHP), mono(2-ethyl-5-carboxypentyl) phthalate (MECPP) and mono(2-ethyl-5-hydroxyhexyl) phthalate (MEHHP) metabolites of di-(2-ethylhexyl) phthalate (DEHP) detected in over 90% of NHANES participants; [22] methyl paraben, ethyl paraben, propyl paraben, and butyl paraben, found in 90% of NHANES participants, [76] and benzophenone-3 (BzP-3), detected in 97% of NHANES participants [62].

We will analyze urine samples by Liquid Chromatography Mass Spectrometry (LCMS) for the presence of the target metabolites listed above. All targets have commercially available isotopically labeled standards, called “surrogates.” The isotopically labeled surrogates will be spiked into the urine before sample preparation. The level of the surrogates will be determined during method verification. Sample preparation will consist of solid phase extraction per the protocol established during method verification. A solvent blank will be prepared concurrently. An internal standard will be spiked into each sample and blank after extraction. Native target response, if detected, will be reported as a ratio to the isotopically labeled surrogate. Two replicates will be run per sample to ensure reproducibility and repeatability as part of the quality control and assurance. Results will be reported to MM including sample ID, date received, date analyzed, metabolite levels, limit of quantification and detection, as well as specific gravity (to adjust for individual hydration status).

After analyzing the samples, we will calculate the percentiles (25^th^, 50^th^, 75^th^ and 95^th^) of analyzed samples and compare participants’ levels for each of the metabolites with existing MM users, as well as the national averages derived from NHANES. Participants’ metabolite levels will be categorized into low (below 25^th^ percentile), medium (equal or above 25^th^ to 75^th^), high (equal or above 75^th^ to 95^th^), and very high (equal or above 95^th^). For the intervention group, MM will also audit their lifestyle behaviors and products used. Problematic areas, such as handling thermal receipts, consuming canned food or drinks, and using products with fragrance, the presence of other harmful ingredients, etc. will be listed in the report along with the lab results and comparisons. The MM team will also be blinded to participants' identifiable information to ensure no bias is introduced. A detailed list of personalized behavior and product recommendations will be provided to the participants for them to follow and make changes. The control group will receive generalized recommendations, based on their exposure levels, that cover multiple areas, including diet, home environment, personal and household products, etc. The same process will be performed for the second kits. EDC levels from participants at baseline (first test) and second test will be compared, and factors such as food, diet, product use, health status, and stress and physical activity levels will be correlated with changes in EDC exposures. Covariates, including sex, BMI, age, education level, household income, and social support will be included in the analysis.

For the analysis plan, we will examine the distribution and concentrations of each of 13 chemical analytes in urine to determine geometric means, medians, percentiles and ranges of exposures. We will compare the percentiles with those reported in the NHANES study. We will include BMI, age, gender, diet, education and household income as covariates. Participants’ dietary patterns will be captured prior to sample collection by looking at their consumption of packaged food and times eating out as these are important culprits of EDC exposures. We will conduct an intent-to-treat analysis. The primary outcomes are the pre-post (first and second tests) differences in specific gravity-adjusted concentration levels per analyte. Clinical biomarkers measured before and after the intervention will also be compared to assess improvement in health and reduced disease risk. We willassess changes in participants’ EHL, RtC and well-being before and after the interventions as well. We will first generate summary statistics on participants’ responses. Changes will be calculated based on paired values of individual responses.

For all analyses, data will be reviewed to ensure assumptions are not violated. If outcomes are not sufficiently normally distributed for parametric tests to be valid, nonparametric tests will be conducted. If needed, variables with response categories with too few participants will be combined. Attrition analyses will be run to compare demographic variables between participants who completed post-test surveys and those who did not.

Summary data and associations between demographic variables and EHL, RtC, well being, EDC metabolites, and clinical biomarkers will be analyzed for all participants with pre-test survey data. Independent sample t-tests, one-way ANOVAs, Chi-square tests, and Spearman’s rank correlations will be run as appropriate. Changes from pre-test to post-test comparing differences between the intervention and control groups, will be analyzed for participants who completed both surveys using regression analyses, controlling for significant demographic variables.

We have established a data monitoring committee for this study, which includes statisticians, chemists, and epidemiologists. Ongoing (weekly) project oversight will occur by the project PI ([name]) in conjunction with [name]. In addition, our MM’s Chief Technology Officer, who has extensive experience in the fields of internet security, computer science, and HIPAA regulations—will participate in the project’s Data and Safety Oversight Committee, which will meet at regular intervals (e.g., semi-annually or more frequently as indicated) throughout the project period to provide input and feedback related to study recruitment, data completion rates, measurement issues, and adverse events*. *MM and HNP will have access to the final trial dataset. Personal information from enrolled participants will be stored separately from results to protect confidentiality, and deidentified data will be shared with participants after the trial.

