### Surveys, study measurements and secondary outcomes

EDC levels will be measured at baseline and 3 months. Participants' age, level of education, income, BMI, self-assessed health status, smoking status, alcohol intake, exposure to other toxic substances (e.g. dangerous chemicals, radiation), will be collected via questionnaires after recruitment to the study. We will measure participants’ environmental health literacy (EHL), readiness to change (i.e. readiness to reduce exposures, RtC), and well-being (general health, social support, financial well-being, sleep, stress, and physical activity) at baseline, 3 months (post-intervention surveys), and 6 months (exit surveys) after baseline (see Fig. 1). We will also assess usability and participant satisfaction 3 months after baseline (post-intervention). The EHL survey was adapted from the framework of the “general environmental health scale” section of the survey by Lichtveld et al. [66] which was validated in two geographic areas via exploratory and confirmatory factor analysis. Questions include those regarding individuals’ environmental health knowledge (e.g. “Household dust contains harmful chemicals”), attitudes (e.g. “I am concerned about chemicals I am exposed to through products I buy”), and behaviors (e.g. “I take steps to avoid inhaling cleaning products”). We adapted the RtC survey based on the Transtheoretical Model of Health Behavior Change [67] in which we ask about current efforts and interest in limiting exposure to harmful chemicals. EHL and RtC will be assessed to determine their association with EDC levels, as well as the effect of the intervention on EHL and RtC.

We will also measure participants’ well-being via relevant questions from three validated surveys. General health and sleep will be assessed using questions from the Behavioral Risk Factor Surveillance System; [68] stress will be measured via the Perceived Stress Scale (PSS), [69] and physical activity will be assessed using the International Physical Activity Questionnaire [70, 71]. These secondary health outcomes will be measured at baseline, 3-month and 6-months later to assess changes.

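### Three covariate rules disagree, and two of the named covariates (diet and social support) are intervention targets not tied to baseline

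*Protocol article*

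**What the plan says.** All three rules stand in the protocol article under *Data collection, management, and analysis*.

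- After the sentences on comparing first and second EDC tests and correlating lifestyle factors with change: "Covariates, including sex, BMI, age, education level, household income, and social support will be included in the analysis". Diet is not listed.
- In the analysis-plan paragraph, shortly before the intent-to-treat and primary-outcome sentences: "We will include BMI, age, gender, diet, education and household income as covariates". Social support is not listed.
- For pre-to-post changes compared between arms, among those who completed both surveys: "using regression analyses, controlling for significant demographic variables". No test or threshold is given.

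On how diet is measured, the article says that "dietary patterns will be captured prior to sample collection by looking at their consumption of packaged food and times eating out". It names neither the visit nor the arm. There are two urine samples, at baseline and at 3 months. On the only food record it describes, it says "For the intervention group, MM will also audit their lifestyle behaviors and products used". Under the test-kit heading, controls start at the step after the audit.

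*Surveys, study measurements and secondary outcomes* places social support among the measured outcomes, "well-being (general health, social support, financial well-being, sleep, stress, and physical activity", at baseline, 3 months and 6 months. The questionnaire items listed there do not include diet.

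**The concern.** The three rules cannot all be followed in one model, and the article does not say which governs the comparison the trial exists to make. If the third rule covers only survey outcomes, as its reference to survey completers suggests, the two lists are the only adjustment stated for the metabolite primary outcomes. If it covers everything, the primary model depends on which demographic variables turn out significant.

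The lists matter because of what is in them. Diet is defined by packaged food and eating out, and classes 5 and 6 in Table 1 deal with processed food, food packaging, cooking and ordering food. *Previous work* reports these same two behaviours shifting after report-back: of 50 people with final surveys, 20% dined out less and 32% ate less packaged food. Social support is a behaviour-change technique named under *Report-back and curriculum*, and the forum and coaching are meant to supply it.

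A post-baseline value of either variable lies on the path from arm to outcome. Adjusting for it removes part of the effect under test. If diet were recorded only through the audit, a complete-case model containing diet could not compare the arms at all.

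**Working it through.** **1. The rules side by side**

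| Rule | Diet | Social support | Demographics | Time point |
|---|---|---|---|---|
| First list | no | yes | fixed | not given |
| Second list | yes | no | fixed | not given |
| Between-arm regression | not demographic | not demographic | by significance | not given |

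Sex or gender, age, BMI, education and household income are common to both lists. The disagreement is over diet, social support and selection.

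**2. Does adjusting for diet matter?** The article gives no figure on this point to reproduce, so the check is an illustration under stated assumptions.

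Inputs from the article:
- 150 analysed per arm (*Sample size*, after 50% attrition).
- An effect of 0.37 SD. *Clinical biomarker testing* states this for free testosterone; it is borrowed here only as a scale.

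Assumed inputs:
- Diet-outcome slope 0.4.
- Coefficient of 0.6 from baseline to 3-month diet.
- A share *s* of the effect acting through diet, with *s* = 0.25, 0.50 or 0.75.

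Model: 3-month diet = 0.6 × baseline diet + *a* × arm + noise, with *a* = *s* × (−0.37)/0.4. Outcome = −0.37(1 − *s*) × arm + 0.4 × 3-month diet + noise. The fit was least squares, two-sided alpha 0.05, 2,000 replicates.

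Adjusting for 3-month diet should leave −0.37(1 − *s*): −0.278, −0.185 and −0.093. The simulation agrees (estimate in SD, then power):

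| *s* | No diet term | Baseline diet | 3-month diet |
|---|---|---|---|
| 0.25 | −0.374, 0.894 | −0.373, 0.904 | −0.279, 0.740 |
| 0.50 | −0.366, 0.886 | −0.365, 0.904 | −0.180, 0.370 |
| 0.75 | −0.371, 0.893 | −0.369, 0.910 | −0.090, 0.134 |

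Baseline diet recovers the effect. With an added unmeasured cause of both 3-month diet and outcome (coefficient 0.3 on each) and *s* = 0.50, the estimate adjusted for 3-month diet was −0.144. The direct effect is −0.185, so that model does not recover even the direct effect.

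On a concentration scale, take an assumed true reduction of 25%: ln(0.75) = −0.288. Removing 30% gives exp(−0.201) = 0.818, an 18% reduction. Removing 50% gives exp(−0.144) = 0.866, a 13% reduction.

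**3. Does selection by significance bias the arm effect?** Six baseline covariates were simulated, each correlated 0.10, 0.15 or 0.25 with the outcome. They were kept if p < 0.05, either for association with the outcome or for imbalance between arms.

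- Estimates under selection ran from −0.363 to −0.373 against a true −0.37.
- Type I error ran from 0.037 to 0.055, with Monte Carlo error √(0.05 × 0.95/2000) = 0.005.
- The visible cost was power: at correlation 0.25, selecting on imbalance gave 0.911, against 0.986 with all six covariates fixed in advance.

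**The case against.** The strongest reply is that the article never says diet or social support enters the arm comparison. The sentence that does compare the arms speaks of demographic variables, and neither is one. The first list follows a sentence about correlating factors with exposure change, and the second follows descriptive statements about analyte distributions, so the lists may serve other analyses. Table 2 also sends statistical methods, adjusted analyses and analysis populations to Appendix 2, which is not shown and may settle timing and model-by-model lists.

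Much of this stands, and it limits what can be claimed. A reader might infer any of four stronger things:

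- **That a second-kit diet value is the covariate.** The article says the process is repeated for the second kit, which makes a second value possible. It does not say which value is used.
- **That social support is not measured in both arms.** It is surveyed in participants generally at baseline, 3 and 6 months. Only its time point as a covariate is open.
- **That diet is missing in all 300 controls.** This is inferred from the intervention-only audit and the absence of a diet item in a condensed questionnaire list. The sentence on dietary patterns is not limited to one arm.
- **That selection by significance biases the arm effect.** The check above shows no material bias.

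A single mediated share for all 13 analytes is also implausible, since the background ties some of them mainly to personal care products. Controls receive dietary recommendations too, so only the between-arm difference in diet change could mediate.

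The reply does not remove the contradiction. The article prints differing lists and a data-driven rule, and the second list stands close to the primary-outcome statement. An appendix may add detail, but published rules that conflict still have to be reconciled.

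**Conclusion.** The concern holds in a limited form. The three covariate rules disagree. Two named covariates are things the intervention acts on, one of them is also an outcome, and neither is restricted to baseline. Whether diet is measured in the same way in controls is unclear.

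Any loss of effect is conditional: it arises only if post-baseline values are used in the arm comparison. Its size cannot be read from the article. Under the assumptions above it runs from a quarter to three quarters of the effect, simply because those are the shares assumed. Baseline values measured alike in both arms would do no harm. Selection by significance leaves the model open to choice after the data are seen and can cost some precision, but it is not a source of material bias.

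**What to change.** For the arm comparison of the primary metabolite outcomes, state one prespecified covariate set: arm, baseline value of the outcome, sex, age, BMI, education and household income. Delete the word *significant* from the regression sentence, and bring the two lists into line with this set.

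Admit diet or social support only as baseline values collected in the same way in both arms; otherwise leave them out. Keep 3-month diet, product use and social support for a separate mediation or exploratory analysis, labelled as such.

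The cost is a wording change in the protocol and analysis plan. If diet is wanted for the mediation analysis and is not already asked of controls, two or three identical items on packaged food and eating out can be added to an existing survey for both arms. *Trial status* says study events began in September 2024, so if controls already past baseline were not asked, their baseline diet can no longer be collected prospectively. That is a practical reason to leave diet out of the primary model.

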
These EDCs have relatively short half-lives in the body (i.e. 6 hours to 3 days) [41–43]. Therefore, the fact that most of the population is exposed at any one time [5, 6] indicates ubiquitous and constant exposure sources. However, the rapid elimination from the body also allows for reduction of internal exposure with removal or avoidance of the exposure sources from daily life. Thus, interventions aimed at identifying exposures (through internal and external assessments) and removing them (via personalized recommendations based on exposure levels and lifestyle habits), have the potential to greatly reduce transient EDC exposures, as demonstrated in our previous work [44].

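### The primary urine analysis compares pre-post change without the baseline concentration as a covariate and with a normality-triggered switch of test; a prespecified baseline-adjusted log-scale model would be more precise on data already collected

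*Protocol article*

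**What the plan says.** The section on data collection, management, and analysis defines the primary endpoint: "The primary outcomes are the pre-post (first and second tests) differences in specific gravity-adjusted concentration levels per analyte". It names no log or other transformation for this difference. Skewness enters only descriptively, where each analyte is to be summarised "to determine geometric means, medians, percentiles and ranges of exposures".

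The same section gives two covariate lists. One reads "We will include BMI, age, gender, diet, education and household income as covariates"; the other reads "Covariates, including sex, BMI, age, education level, household income, and social support will be included in the analysis". Neither names the baseline concentration. The one sentence that describes the between-arm comparison says that changes will be "analyzed for participants who completed both surveys using regression analyses, controlling for significant demographic variables". Baseline concentration is not a demographic variable.

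The choice of test is conditional on the data: "If outcomes are not sufficiently normally distributed for parametric tests to be valid, nonparametric tests will be conducted". No threshold, specific rank test or transformation is given.

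The baseline value is available. Under the surveys and study measurements heading, "EDC levels will be measured at baseline and 3 months", and the intervention design section sends a baseline kit to all participants.

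**The concern.** A change score subtracts the whole baseline value. That is efficient only if baseline predicts follow-up with a slope near one. When the correlation is lower, the subtraction adds baseline noise to the outcome. A lower correlation is plausible here: "These EDCs have relatively short half-lives in the body (i.e. 6 hours to 3 days", each time point rests on a first-void sample, and the tests are three months apart. A chance imbalance in baseline levels between arms would also pass into the unadjusted result through regression to the mean. The trial plans for half of each arm to be lost, so imbalance among those retained is a real possibility.

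The scale matters too. If the difference is taken in concentration units and the data are right-skewed, a few very high values carry much of the weight. The plan's remedy is to change the test after looking at the distribution. Across 13 analytes this could leave some reported as regression coefficients and others as rank tests, with no common measure of effect.

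What is at stake is precision on every primary endpoint and a result that can be compared across the panel. The sample size section gives no effect size, SD, alpha or power for the metabolites, so no documented margin absorbs a loss.

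**Working it through.** **The plan's own figure.** The only calculation with complete inputs is the one for free testosterone: paired t-test, two-sided 0.05, 95% power, effect 0.37. It reproduces: the noncentral t gives n = 97, and 97 x 1.3 = 126. It concerns a blood biomarker, not the urine endpoints. For those, the plan gives only 300 x 0.5 = 150 per arm, so there is no power figure to reproduce.

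**Inputs.** n = 150 per arm (sample size section). The correlation r, the geometric SD and the effect are not in the documents and are assumed below.

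**Step 1, same scale.** With SD s at both time points:
- variance of change = s² + s² - 2rs² = 2(1-r)s²
- residual variance after adjusting for baseline = (1-r²)s² = (1-r)(1+r)s²
- ratio = 2/(1+r), so the efficiency lost by the change score is 1 - (1+r)/2 = (1-r)/2

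The last column gives power for a difference of 0.3 s at 150 per arm (normal approximation, two-sided 0.05).

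| r (assumed) | Variance ratio | Loss | Adjusted n per arm matching 150 on change | Power, change to adjusted |
|---|---|---|---|---|
| 0.2 | 1.67 | 40% | 90 | 54% to 76% |
| 0.4 | 1.43 | 30% | 105 | 66% to 81% |
| 0.6 | 1.25 | 20% | 120 | 83% to 90% |
| 0.8 | 1.11 | 10% | 135 | 98% to 99% |

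The direction does not depend on equal variances. If the follow-up SD is ks, the change score has variance (1 + k² - 2rk)s² and the adjusted analysis k²(1-r²)s². They differ by (1-rk)²s², which is never negative.

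**Step 2, the change outcome can stay.** If y = a + b(arm) + cx, then y - x = a + b(arm) + (c-1)x. Regressing log change on arm and log baseline therefore gives the same treatment effect b. What is missing is the baseline term, not a different outcome.

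**Step 3, scale and test.** A simulation used log-normal data, a 30% lower geometric mean in the intervention arm, 150 per arm and 1,500 runs per scenario. Power at r = 0.2 / 0.4 / 0.6:

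| Method | Geometric SD 2.5 | Geometric SD 3.5 |
|---|---|---|
| t-test, untransformed change | 47 / 55 / 69% | 20 / 25 / 30% |
| Mann-Whitney, untransformed change | 63 / 74 / 88% | 36 / 47 / 61% |
| t-test, log change | 77 / 86 / 96% | 48 / 62 / 77% |
| Log scale, baseline-adjusted | 94 / 95 / 98% | 70 / 77 / 86% |

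The last two rows isolate the baseline term. In a run with no effect (geometric SD 3, r = 0.4), every method in the table rejected in 4.5% to 5.7% of trials, so the gain is not bought with inflated type I error. The conditional switch itself was not simulated.

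**The case against.** The strongest reply is that much of this is read from silence. The article does not say that the difference is untransformed, and planned geometric means fit a log analysis as well as any other. One covariate list is open-ended, and the other follows a descriptive comparison with national data. The SPIRIT table refers the statistical methods to an Appendix 2 that is not shown and may supply both the log scale and the baseline term. This stands as a limit: a reader might infer that the plan commits to raw differences and rules out baseline adjustment, and the text does not support that. But it does name a change outcome and controls that are only demographic, and that wording would still need reconciling with the appendix.

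A reader might also infer that the trial wastes 30% to 40% of its sample, or has 20% to 69% power. Neither is supported. Both need an assumed r or SD. The article also describes exposure sources as ubiquitous and constant, which points towards a higher r and a smaller loss. The lowest powers belong to a t-test that the plan's own nonparametric clause would largely replace, and log-normal data with a proportional effect favour the log model.

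Nor is it right that rank methods cannot carry covariates or give estimates: rank ANCOVA and Hodges-Lehmann estimates exist. The article simply names neither. Blinding of the analysts also limits arm-driven choice of test.

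Finally, the change is not entirely free of consequences. The trial is registered and has been recruiting since July 2024, the estimand changes, and detection is below 100% (89% is cited for BPS and BPF).

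**Conclusion.** The point holds as a matter of precision and prespecification. Change scores with demographic-only adjustment, and a data-triggered move to unspecified rank tests, are less precise than a baseline-adjusted analysis of the same samples. With equal variances this holds for every r below 1. The size is uncertain: 10% to 40% of efficiency over r = 0.8 down to 0.2, all assumed. The further gain from the log scale depends on the data being close to log-normal and on the planned difference being untransformed, which the article does not settle. This does not show that the planned analysis is biased or invalid. It should be corrected before unblinding.

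**What to change.** For each analyte, make this the prespecified primary model: log specific gravity-adjusted 3-month concentration on arm and log specific gravity-adjusted baseline, plus covariates fixed in advance, such as sex. Regressing log change on the same terms is equivalent. Report the ratio of geometric means with its 95% confidence interval. Remove the normality-triggered switch and keep a rank-based analysis as sensitivity.

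For the continuous EHL and well-being scores, add the baseline score as a covariate. RtC is adapted from a stage model and needs a method suited to ordinal data.

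If Appendix 2 already contains these terms, reconcile the article's wording with it.

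The cost is wording; no new measurement is needed. Two small downsides must be handled: the estimand becomes a ratio of geometric means, to be specified before unblinding, and a rule for values below the detection limit has to be stated.

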### Sample size

We will recruit and randomize 600 participants (1:1 male to female). According to previously published research, this has the power to detect estimated effect sizes for 13 endpoints (9 metabolites and 3 survey analyses), [6, 44, 56, 60, 61] from a sample of *n* = 150 participants per arm (i.e., after 50% attrition down from the original *n* = 300 per arm).

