### Intervention design

Upon consenting and randomization, all participants will be sent baseline surveys and test kits (for baseline urinary exposure levels, and, for a subset, clinical biomarkers). The control group (n = 300) will complete post-test surveys and use the second kits approximately 3 months after the baseline assessment, while the intervention group (n = 300) will complete a Lifestyle Audit and engage in the 8-week curriculum described above. The intervention group will submit the kits 2 weeks after completion of the curriculum (i.e. 3 months after the baseline test). See Fig. 1 for the control vs. intervention group study events.

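### The protocol promises intent-to-treat but limits the between-arm comparison of change to participants who completed both surveys, in a trial that plans for 50% attrition

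*Protocol article*

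**What the plan says.** In the protocol article, *Data collection, management, and analysis* states: "We will conduct an intent-to-treat analysis". It defines the primary outcome in urine: "The primary outcomes are the pre-post (first and second tests) differences in specific gravity-adjusted concentration levels per analyte". On survey responses it adds: "Changes will be calculated based on paired values of individual responses".

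The last paragraph of the analysis plan opens by listing literacy, readiness, well-being, EDC metabolites and clinical biomarkers. It then gives the only between-arm model in the article: "Changes from pre-test to post-test comparing differences between the intervention and control groups", which "will be analyzed for participants who completed both surveys using regression analyses, controlling for significant demographic variables".

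*Sample size* bases power on 150 participants per arm, "after 50% attrition down from the original" 300.

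Timing of the second measurement is described in two ways. *Intervention design* places the control arm at about 3 months after baseline, but for the other arm says: "The intervention group will submit the kits 2 weeks after completion of the curriculum (i.e. 3 months after the baseline test". *Data collection, management, and analysis* says, without distinguishing arms: "Three months after submitting their baseline urine sample, participants will be sent the second kit".

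The SPIRIT checklist (Table 2, item 20c) refers the analysis population and missing data to Appendix 2, which is not shown.

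**The concern.** Intent-to-treat means that everyone randomised is compared in the arm to which they were assigned. Restricting the comparison to people who returned the post-intervention survey selects on something that happens after randomisation and that the intervention may influence. The groups compared are then no longer the groups that randomisation formed.

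The arms ask different things of participants. Only the intervention arm must complete at least 6 of 8 classes within 8 weeks (curriculum section) and attend at least 3 coaching sessions (*Online coaching and community forum*). Staying in the study may therefore depend on motivation or early success more in one arm than in the other. If so, the completer comparison mixes the effect of the programme with the difference in who stayed. At stake are the primary urine comparison, if the rule covers it, and the literacy, readiness and well-being comparisons in any case.

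**Working it through.** **1. Planned loss.** Inputs from *Sample size*: 300 randomised per arm, 50% attrition.

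300 × (1 − 0.50) = 150 per arm, which reproduces the plan's figure. Over both arms, 2 × 150 = 300 of 600 remain and 300 are lost. *Previous work* makes heavy loss credible: 424 people completed surveys before the intervention and 174 after it (174/424 = 41%), and 55 gave a second urine test.

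**2. Whom each rule keeps.** Under intent-to-treat all four rows below belong to the analysis set. Under the survey rule it depends on how far the sentence reaches:

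| Second urine | Post-survey | Rule covers urine | Rule covers surveys only |
|---|---|---|---|
| yes | yes | in | in |
| yes | no | observed urine change discarded | urine kept, survey outcomes dropped |
| no | yes | no urine change, surveys in | no urine change, surveys in |
| no | no | out | out |

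The second row is where the rule itself discards primary-outcome data. The documents do not say how many participants will fall there. On the narrower reading the article describes no between-arm model for the primary outcome, and the conflict persists for the survey outcomes.

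**3. What selective retention could do (assumed, not from the documents).** Take one continuous outcome with no true effect and 150 of 300 retained in each arm. Control dropout is unrelated to outcome. In the intervention arm, the tendency to stay has correlation r with the outcome change.

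- Bias in SD units: b = r × √(2/π) = 0.798 r
- Variance among those retained: v = 1 − 0.637 r²
- Standard error: SE = √((v + 1)/150)
- Two-sided type I error: Φ(b/SE − 1.96) + Φ(−b/SE − 1.96)

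For r = 0.2: b = 0.160, v = 0.975, SE = √(1.975/150) = 0.115, b/SE = 1.39, type I error = 28.5%.

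| r | Bias (SD) | Type I error, formula | Simulated (4,000 trials) |
|---|---|---|---|
| 0 | 0 | 5.0% | 4.8% |
| 0.1 | 0.08 | 10.6% | 10.1% |
| 0.2 | 0.16 | 28.5% | 29.0% |
| 0.3 | 0.24 | 55.7% | 56.4% |

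For scale, the difference detectable with 80% power at 150 per arm is (1.960 + 0.842) × √(2/150) = 0.32 SD. A negative r gives the same error rates with the bias against the intervention. Both arms lose exactly half in this example, so equal attrition percentages do not remove the problem.

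**4. Timing.** An 8-week curriculum plus 2 weeks is 10 weeks from its start, and 3 months is about 13 weeks. The two descriptions in *Intervention design* therefore agree for someone who starts about 3 weeks after the baseline test and finishes on schedule. They part for someone who finishes late or not at all. The test-kit section, *Surveys, study measurements and secondary outcomes* and *Data collection, management, and analysis* all use 3 months, with no completion condition.

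**The case against.** The strongest reply has four parts.

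- **Scope.** The restricting sentence speaks of surveys and of pre-test and post-test, while the article calls the urine measurements first and second tests. It may govern survey outcomes only. That reading is open. It leaves the conflict in place for those outcomes, and the text needs to say which reading is meant.
- **Appendix 2.** Analysis population and missing data are referred to a document not shown, so it would be wrong to say that the trial has no missing-data method. This stands. The point rests on two statements in the published text, however, and an appendix can agree with only one of them.
- **Attrition versus rule.** A reader might infer that the survey rule removes 300 of 600 participants. It does not: 300 is the planning allowance for attrition, and someone without a second sample has no observed pre-post difference under any rule.
- **Bias.** A reader might infer that completers in the intervention arm are the most motivated, so the result favours the intervention, perhaps by a factor of two. The factor of two requires that every intervention dropout gains nothing, which the documents do not say. They also give reasons for retention to hold up: payment for completing study steps (*Participants*) and coaches who contact intervention participants on their own initiative. Differential dropout is a possibility, not an established fact.

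A further tempting reading is that an intervention participant who does not finish the curriculum has no outcome time or is refused a kit. The parenthesis in *Intervention design* and the other 3-month statements give everyone a test time, and nothing says a kit is withheld.

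**Conclusion.** The contradiction is real and stands on the text alone: intent-to-treat is declared, and the only between-arm model described is confined to those with both surveys. Its importance comes from the planned 50% attrition, which makes the choice of analysis set a question about half of those randomised.

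Whether the rule reaches the primary urine outcome is ambiguous. The number of participants whose urine data it would discard is not given. The size and direction of any bias cannot be derived from the documents. The type I error range of about 11% to 56% for r from 0.1 to 0.3 shows sensitivity under stated assumptions and is not a forecast. The timing discrepancy is a smaller matter of wording, but it bears on whether both arms are measured alike. The text should be corrected before the analysis is carried out.

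**What to change.** 1. Delete the both-surveys restriction for the arm comparison. Define the primary set as all randomised participants in their assigned arm.
2. State that every available urine result is used whether or not surveys were returned, and name the between-arm model for the urine outcome.
3. Include baseline-only participants through a stated missing-data method consistent with Appendix 2. Urine has only two time points, so a likelihood model that assumes data missing at random will move the urine estimate little from the completer result. A missing-not-at-random sensitivity analysis, for example control-based imputation, is therefore needed. The survey outcomes also have a 6-month measurement that the model can use.
4. Keep the both-survey analysis as a labelled secondary analysis. The planned demographic comparison of completers and non-completers can stay as description.
5. Reconcile *Intervention design* with the 3-month statements elsewhere by saying that the second kit and post-survey go to all participants in both arms at the same time from baseline, whether or not the curriculum was completed.

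The cost is protocol and SAP wording, a modest amount of analysis work and a common mailing date. No extra participants are needed.
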